### Data analysis and processing

A tri-axial accelerometer (Trigno^™^ Wireless System, Delsys, Inc., Natick Massachusetts, USA), sampling at 148.15 Hz, will record the center of mass acceleration during gait assessments. EMGWorks^®^ 4.7.5 (Delsys, Inc., Natick, Massachusetts, USA) will be used for data collection. Gait parameters will be derived from vertical acceleration data algorithms previously validated [52, 53] in the Matlab^®^ R2022b software (The MathWorks, Inc., Natick, Massachusetts, USA). In summary, the acceleration data will be transformed using a vertical-horizontal coordinate system and filtered with a 4th-order Butterworth filter, having a cutoff frequency of 20 Hz [54, 55]. The initial and final contacts of the gait cycle will be estimated using the continuous wavelet transform (CWT) of vertical acceleration. The initial and final contact events will be identified through the minimum and maximum points of the CWT, respectively [52]. Step velocity, step time, step length, and swing phase will be calculated. Additionally, the variability of each gait parameter will be calculated by the coefficient of variation.

PFC activity will be registered using a mobile 8-channel fNIRS device (OctaMon Artinis Medical Systems, Elst, The Netherlands), with a collection frequency of 10 Hz. The Octamol model is equipped with eight light transmitters and two light detectors (four transmitters and one detector per hemisphere), that detect changes in concentrations of oxygenated (HbO_2_) and deoxygenated (HHb) hemoglobin. This system employs infrared light with wavelengths of 760 and 850 nm and an interoptode distance of 35 mm. The OctaMon model utilizes a Bluetooth connection, enabling participants to walk without the inconvenience of wires. OxySoft 3.0.52 software (Artinis Medical Systems, Elst, The Netherlands) will be used for data collection, storage and calculation of HbO_2_ and HHb concentrations. The modified Beer-Lambert law will be applied to convert the optical density of the raw signal into HbO_2_ and HHb concentrations. The differential path factor will be set to 6.61 for all participants.

The fNIRS signal analysis procedures (artifact corrections and filtering) will be carried out using the open-source software NIRS-SPM (http://www.fil.ion.ucl.ac.uk/spm/software/) [56] following previous recommendations [57]. In summary, a low-pass filter based on the canonical hemodynamic response function will be used to reduce high-frequency noise. Additionally, a wavelet algorithm will decompose the signal into global trends, hemodynamic responses, and movement artifacts. Preprocessed data will be exported to Matlab^®^ R2022b software, and a customized algorithm will be used for additional processing. HbO_2_ and HHb concentrations will be analyzed for each hemisphere separately (interpreted by stimulated and non-stimulated). The means of these parameters will be calculated considering four channels per hemisphere. Subsequently, data analysis will be divided into baseline and task periods. The baseline period will consist of 10 s before starting walking, and the task period will be from the 5th to the 25th second after starting walking. The mean concentrations of HbO_2_ and HHb will be calculated for each period, and the differences between periods for each parameter will be utilized to evaluate the relative change in cortical activity.

### Statistical analysis

Statistical analysis will be conducted using SPSS 25.0 software (International Business Machines Corporation, Armonk, New York, USA), with a significance level set at *p* < 0.05. Clinical, cognitive, and demographic characteristics will be summarized using means and standard deviations or medians and quartiles (25–75) based on the normality of data distribution. The side effects of tDCS will be analyzed with Friedman’s ANOVA. Means and standard deviations will be calculated for primary, second, and intervention outcomes (treadmill velocity and total distance covered, SPE, and percentage of HRmax). Two-way ANOVA with repeated measures for stimulation (M1 x multitarget x PFC x sham) and moment (pre and post) will be employed to analyze gait parameters and activity cortical in each walking condition separately (usual, obstacle avoidance, and dual task). The Mauchly test will be used to check sphericity, and the Greenhouse-Geisser correction will be adopted if necessary. In the case of interaction between factors, Bonferroni post hoc tests with adjusted significance levels will be utilized to identify differences. Finally, for each combination of AE and tDCS, the Standardized Response Mean will be calculated as the effect size of the intervention, considering the mean difference between moments (post—pre) divided by the standard deviation of change.

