## Materials and method

### Study design and setting

A randomized, crossover, double-blind, sham-controlled clinical trial will be conducted at the Posture and Gait Studies Laboratory (LEPLO) of São Paulo State University (Unesp), Institute of Biosciences, Rio Claro. This study protocol adheres to the Standard Protocol Items: Recommendations for Interventional Trials (SPIRIT) checklist (S1 Checklist) [37]. The project was approved by the research ethics committee of the same University (CAAE: 54476421.1.0000.5465) and is registered on the Brazilian Clinical Trials Registry platform (RBR-738zkp7) with the Universal Trial Number (UTN) code U1111–1277-3248. Other documents on ethical appraisal can be found in the supporting information (S1–S4 Files). PwDP will visit the laboratory for non-consecutive five days, with screening assessments and treadmill familiarization conducted during the first visit. During the remaining four visits (minimum of one week apart), participants will undergo pre- and post-assessments (gait and cortical activity) and a session of AE combined with anodal tDCS (applied on M1, PFC, multitarget, or sham condition). All experimental procedures will be performed at the same time of the day for each PwPD and during the ON state of Parkinson’s disease medication. Fig 1 shows a SPIRIT diagram for the timeline of procedures.

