### Participants

#### Sample recruitment and selection

This study will employ the convenience sampling technique, selecting, and recruiting PwPD from the community-dwelling. The sample size was calculated in G*Power software version 3.1, based on data from Fernandez-Lago colleagues [35]. The primary outcome and statistical tests used were gait velocity and Two-way ANOVAs with repeated measures (within factors), respectively (alpha = 0.05; beta = 0.08; ηp^2^ = 0.43). The sample size analysis indicates a minimum of 16 PwPD is required for this study. Considering the potential for sample loss, we will invite 24 PwPD to participate in the clinical trial through personal and/or telephone contact (from November 10^th^, 2023, to March 31^st^, 2024). In case we have a positive reply, a member of the research team will explain the study’s objectives, risks, benefits, and ethical implications. If participants consent to participate in the study, they will be asked to sign two copies of an informed consent form (one for themselves and the other for the member of the research team).

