### Randomization and blinding

The order of intervention sessions will be randomized and counterbalanced across participants in a 1:1:1:1 ratio using an online random number generator (www.randomization.com). A member of the research team, not involved in the experimental procedures, will conduct the randomization, and maintain allocation confidentiality until the session begins. Two strategies will be implemented to ensure study blinding: i) participants will be unaware of the type of stimulation applied in each session and ii) the team member conducting the AE and tDCS sessions will not participate in the pre-and post-assessments.

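### The planned stimulation-by-moment test is a change-score analysis with the baseline slope fixed at 1 and no session term: valid, but less precise than the trial's own data allow

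*Protocol article*

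**What the plan says.** In the Protocol article, *Statistical analysis* gives the model: "Two-way ANOVA with repeated measures for stimulation (M1 x multitarget x PFC x sham) and moment (pre and post) will be employed", run separately for each walking condition. Sphericity is checked by Mauchly's test, with the Greenhouse-Geisser correction if needed. Bonferroni comparisons follow an interaction, and a Standardized Response Mean is reported for each stimulation condition.

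*Randomization and blinding* says: "The order of intervention sessions will be randomized and counterbalanced across participants in a 1:1:1:1 ratio". *Study design and setting* gives each of the four intervention visits, at least a week apart, its own pre- and post-assessment.

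*Sample recruitment and selection* sizes the trial on the same kind of test: "The primary outcome and statistical tests used were gait velocity and Two-way ANOVAs with repeated measures (within factors), respectively". It then states "The sample size analysis indicates a minimum of 16 PwPD is required for this study", with 24 invited to allow for losses.

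No term for session, period or sequence is named in the article.

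**The concern.** The trial asks whether the pre-to-post response differs between the three active montages and sham. In the stated model that question is answered by the stimulation-by-moment interaction. Two pieces of information already in the data are not used as well as they could be.

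- **Session baseline.** The pre value enters as a level of moment, so it is subtracted in full. When the pre and post deviations within a session are only moderately correlated, full subtraction adds noise that an estimated slope would avoid.
- **Session number.** Position 1 to 4 is known for every observation and is what the randomisation balances, but the model has no term for it. Any systematic drift of the change over visits stays in the residual.

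At stake is the width of every stimulation contrast and the chance of detecting a real difference between montages, with 16 to 24 people and Bonferroni-adjusted follow-up.

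**Working it through.** **The plan's own figure.** The printed inputs are "alpha = 0.05; beta = 0.08; ηp^2^ = 0.43", so f² = 0.43/0.57 = 0.754 and f = 0.869. The article does not state the G*Power convention, so several were tried with the noncentral F:

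- 1-df within effect, noncentrality (N−1)f²: N = 18 at power 0.92, N = 14 at power 0.80.
- 3-df effect, noncentrality N·f²: N = 22 at power 0.92, N = 16 at power 0.80.

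The stated 16 is thus approached under the first and matched exactly under the second only if power is 0.80. Nothing below depends on which was used; 16 and 24 serve only as the range of N.

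**Step 1: the interaction is a change-score test.** Moment has two levels, so the interaction contrasts are differences between conditions in (post − pre). On simulated data with N = 24, the interaction F and the one-way repeated-measures F on change were both 0.546204, on 3 and 69 df.

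**Step 2: cost of fixing the slope at 1.** Assume equal pre and post variance s². Let rw be the raw same-session pre/post correlation and rb the between-session correlation. After removing each participant's own level, the correlation of session deviations is rho = (rw − rb)/(1 − rb).

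- Contrast variance per participant, change score: 4s²(1 − rw) = 4s²(1 − rb)(1 − rho).
- Contrast variance per participant, slope estimated: 2s²(1 − rb)(1 − rho²).
- Ratio: (1 − rho²)/[2(1 − rho)] = (1 + rho)/2.

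The document gives no rho, so the range is assumed. The N columns multiply 24 and 16 by the ratio, and the standard-error column is its square root.

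| rho | Variance ratio | Standard-error ratio | N matching 24 on change | N matching 16 on change |
|---|---|---|---|---|
| 0.25 | 0.63 | 0.79 | 15 | 10 |
| 0.5 | 0.75 | 0.87 | 18 | 12 |
| 0.75 | 0.88 | 0.94 | 21 | 14 |
| 0.9 | 0.95 | 0.97 | 22.8 | 15.2 |

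**Step 3: cost of leaving out session number.** Let the change drift linearly by d per session, in units of the within-participant residual SD of change. The four values 0, d, 2d and 3d have a sum of squares about their mean of 5d². With balanced orders this all falls into the error term. For N = 24 the inflation is 24·5d²/69 = (24/23)(5/3)d²:

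- d = 0.2: 1.739 × 0.04 = 0.070, about 7%.
- d = 0.4: 1.739 × 0.16 = 0.278, about 28%.

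These drifts are assumed; they total 0.6 and 1.2 SD over four visits. A shift common to pre and post cancels: simulating a common drift of 0.5 pre-value SD per session left the planned error variance unchanged (ratio 0.996 to 1.006).

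**Step 4: effect on power.** Simulated crossover with balanced orders and equal residual variances. One condition is shifted by 0.85 SD of change, that is 0.6 × √2, or 0.6 SD of the difference in change. The comparison model has participant, session, session baseline and stimulation.

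| rho | N = 24, planned → adjusted | N = 16 drawn at random from 24 |
|---|---|---|
| 0.25 | 0.85 → 0.97 | 0.66 → 0.83 |
| 0.5 | 0.86 → 0.94 | 0.64 → 0.74 |
| 0.75 | 0.84 → 0.89 | 0.67 → 0.71 |
| 0.9 | 0.86 → 0.88 (separate run) | not run |

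Those runs have no drift. With d = 0.4 and N = 24, the planned test's power falls to 0.72–0.76 and its type I error to about 0.02. The adjusted model keeps 0.89–0.96 and about 0.05.

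**The case against.** The strongest reply is that this is a valid analysis whose possible loss may be small. Most of that stands.

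- A reader might infer that the plan throws away its baselines or the efficiency of the crossover. It does neither. Each pre value is used, with coefficient 1, and the within-participant comparison is kept in full.
- A reader might infer that practice on the obstacle and dual-task walks contaminates the result. Practice that lifts pre and post alike cancels in the change. Only drift in the change itself matters, and the article gives no evidence of it.
- A reader might fear bias once dropout unbalances the orders. With 24 falling to 16 at random and a total drift of 1 SD of change, a pairwise contrast shifts with an SD of about 0.08 SD of change, against a standard error of 0.35. That is minor.
- Pre and post are measured on the same day by the same method, so rho could be high and the gain slight. This is possible but not established. What counts is the correlation after each participant's own level is removed: a raw rw of 0.9 with rb of 0.8 gives rho = 0.1/0.2 = 0.5, where a quarter of the variance is avoidable.
- A bare mixed model with one residual variance would lose the Greenhouse-Geisser protection. With one condition's residual SD doubled or tripled (assumed) and N = 16, the adjusted model with fixed participant effects had type I error of 0.063–0.073 or 0.081–0.093, while the planned corrected test stayed at 0.043–0.053. Modelling only the post value would also drop the test of moment. Both points shape the fix.

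A separate analysis plan might add a session term, but the article names the model's factors explicitly, and the point concerns what it names. The article already calls the order counterbalanced; prescribing a particular set of sequences would be a design preference, not part of this point.

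**Conclusion.** The concern holds as one of precision, not validity. That the interaction is a change-score test, and that the variance ratio is (1+rho)/2, are exact, the latter under equal pre and post variances. The practical size is not fixed by the document: about 5% to 37% of contrast variance for an assumed rho of 0.9 down to 0.25. Leaving out session number costs nothing if the change does not drift, and about 7% or 28% of error variance under the assumed drifts. With balanced orders that omission makes the planned test conservative, so the documents do not support reading it as inflating false positives. The change is worth making because the data are already collected and the sample is small.

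**What to change.** Make the stimulation comparison a linear mixed model (MIXED in SPSS) on the post value, for each outcome and walking condition:

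- fixed effects: stimulation, session number (1 to 4, categorical), that session's pre value, and the participant's mean pre value, so that within- and between-participant slopes are not mixed;
- random participant;
- residual variances allowed to differ by stimulation condition, or an equivalent safeguard in place of Greenhouse-Geisser, with small-sample degrees of freedom;
- the 3-df stimulation test, followed by the Bonferroni-adjusted contrasts.

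Keep the within-condition pre-to-post estimates and Standardized Response Means as planned.

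The cost is about 4 or 5 error degrees of freedom (session 3, session baseline 1, mean baseline 1) from the 69 available with 24 participants or 45 with 16, plus slightly more modelling work. Allowing unequal variances may cost a little more; the power figures above do not include that. No new data are needed.

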## Discussion

This study outlines a randomized clinical trial protocol designed to examine the acute effects of AE on a treadmill combined with tDCS on spatial-temporal gait parameters and PFC activity in PwPD. Our protocol includes gaits assessments in various contexts, including usual walking, walking with obstacles, and performing a cognitive task while walking. This comprehensive approach allows us to gain a better understanding of the immediate effects of the combined intervention on the gait of PwPD. Additionally, we will compare the effects of different tDCS setups in combination with physical exercise, with a particular emphasis on multitarget stimulation.

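### The only effect size named for results is a within-session Standardized Response Mean, which does not estimate active versus sham tDCS and is not comparable between stimulation types when their SDs of change differ

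*Protocol article*

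**What the plan says.** All the planned statistics are in the Statistical analysis section of the protocol article.

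- **Effect size.** The section closes by stating that "for each combination of AE and tDCS, the Standardized Response Mean will be calculated as the effect size of the intervention". The formula it gives puts the average post-minus-pre change in the numerator and the SD of that same change in the denominator. No other effect size for results is named. The partial eta squared of 0.43 under Sample recruitment and selection is a planning input.
- **Comparison of conditions.** Gait and cortical outcomes go into a two-way repeated-measures ANOVA with four stimulation levels (M1, multitarget, PFC, sham) and two moments (pre, post), separately for each walking condition. Then: "In the case of interaction between factors, Bonferroni post hoc tests with adjusted significance levels will be utilized to identify differences".
- **Descriptives.** Means and standard deviations are planned for the outcomes.

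On the question being asked, Study design and setting says "A randomized, crossover, double-blind, sham-controlled clinical trial will be conducted", and the Discussion says "we will compare the effects of different tDCS setups in combination with physical exercise". The section on the exercise and tDCS protocol gives the same 30-minute treadmill session to all conditions. Only the stimulation during the 20-minute main phase differs.

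**The concern.** A sham-controlled trial asks how much more the outcome changes with active stimulation than with sham. The figure labelled as the effect size of the intervention is instead an uncontrolled pre-post change, one per session. It can be clearly positive in all four sessions when tDCS contributes nothing.

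The article's own Introduction shows that this is a realistic outcome. It reports that a single treadmill session improved gait velocity and stride length, and that tDCS over M1 did not enhance those gains. The same study supplied the data for the sample size.

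The consequence is for reporting. The trial would publish an effect size that does not match its question, and a later trial or meta-analysis would lack the estimate it needs: the active-minus-sham difference with its interval.

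**Working it through.** **Inputs.** From the article: the SRM definition, four conditions with identical exercise, a minimum of 16 participants and 24 invited. The article gives no SRM, SD of change or correlation between sessions, so there is no stated figure to reproduce. The gains, SDs and correlations below are assumptions. The sample size calculation itself does not bear on this point.

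**1. What an SRM contains.** Write the mean change in a session as exercise effect E plus repeat-testing effect R plus stimulation effect S, with S = 0 for sham.

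- SRM, active = (E + R + S) / SD(active)
- SRM, sham = (E + R) / SD(sham)
- Active minus sham change = (E + R + S) − (E + R) = S

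Only the third line isolates tDCS (assuming E and R are the same in every session and add to S). If S = 0, an active SRM is still (E + R) / SD(active), which is positive whenever exercise or practice helps.

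**2. What the separate denominators do** (illustrative values).

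| Gain A / SD A (m/s) | Gain B / SD B (m/s) | SRM A | SRM B | Difference in change |
|---|---|---|---|---|
| 0.06 / 0.06 | 0.06 / 0.09 | 1.00 | 0.67 | 0 |
| 0.06 / 0.06 | 0.09 / 0.09 | 1.00 | 1.00 | 0.03 m/s |

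SRMs can differ when the gains are equal, and agree when the gains differ.

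In simulation, take an equal mean change of 0.5 active-session SD, a sham SD 1.5 times larger and a between-session correlation of 0.5. At n = 16 the average SRM is 0.53 for active and 0.35 for sham. A given active session has the higher SRM in 73% of trials at n = 16 and 78% at n = 24. With equal SDs this would be 50%.

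**3. Precision of one SRM.** The noncentral-t 95% CI for an observed SRM of 0.5 is −0.03 to 1.01 at n = 16 and 0.07 to 0.92 at n = 24. The section names no interval for the SRM.

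**4. Can the contrast be rebuilt from the planned output?** The point estimate can: subtract mean changes, if means are reported by condition and moment. The SD of change can also be recovered as mean change / SRM. The interval cannot, because

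SD(difference)² = SD(a)² + SD(s)² − 2·r·SD(a)·SD(s)

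needs r, the correlation of changes between sessions, and no planned summary gives it. With equal SDs, the 95% half-width in SD units is t × √(2(1 − r)/n):

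| n | t | r = 0.5 | r = 0 |
|---|---|---|---|
| 16 | 2.131 | 2.131 × √(1/16) = 0.53 | 2.131 × √(2/16) = 0.75 |
| 24 | 2.069 | 2.069 × √(1/24) = 0.42 | 2.069 × √(2/24) = 0.60 |

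A reader without the individual data could not tell which column applies. The trial team can compute the interval directly.

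**The case against.** **The conditions are compared, by the ANOVA.** This is correct, and the SRM does not carry the inference. But the section describes the ANOVA and post hoc tests as a means of finding differences and attaches no size or interval to them. The post hoc step runs only after an interaction, so without one the SRMs are the only effect sizes named.

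**The intervention is the combined package, so the label is fair.** An SRM is a correctly defined description of pre-post change under exercise plus stimulation. That stands, and is why it may be kept. It does not make the SRM an answer to a sham-controlled question, since sham exercise sessions produce the same kind of figure.

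**This is a condensed article, and a fuller plan may add the contrast.** It may, and the mere absence of a contrast estimate would not be a finding. The point rests on what the article does state: a chosen effect size that does not match the design.

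**Nothing shows that SDs of change will differ between sessions.** That stands. The mixing of exercise, practice and stimulation does not depend on it.

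**A stronger reading to avoid.** A reader might infer that the four combinations will be ranked by SRM, largely on chance and spread. The article plans no ranking, threshold or selection by SRM. Chance gaps between four SRMs would indeed be wide, but mostly because the trial is small. With four equal true SRMs of 0.6 and correlations from 0.5 to 0, the mean best-minus-worst gap is 0.35 to 0.48 at n = 24 and 0.45 to 0.60 at n = 16. One pooled SD still leaves 0.30 to 0.43 and 0.37 to 0.52. A common denominator therefore removes only a small part of the gap, and the gap is no argument against the SRM in particular.

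**Conclusion.** The point holds as a mismatch between the named effect size and the trial's question. That the SRM does not isolate tDCS follows from the design alone: all four sessions contain the same exercise and the same repeat testing. That SRMs are not comparable across conditions holds when the SDs of change differ. The 1.00 versus 0.67 example and the 73% to 78% figures show the possible size under assumed SDs and are not predictions for this trial.

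The validity of the planned ANOVA is not affected. The estimate that should accompany it would be imprecise at this size: a half-width of roughly 0.42 to 0.75 SD of change, for n from 24 to 16 and correlation from 0.5 to 0. That is a reason to report the interval. The change should be made, and it concerns analysis and reporting, not conduct.

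**What to change.** In the Statistical analysis section:

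1. Name as the reported effect size, for each active condition, the within-participant difference (post − pre, active) − (post − pre, sham), in outcome units (m/s for gait velocity), with a 95% CI, whether or not the interaction is significant.
2. If a standardised version is wanted, divide every comparison by one common SD and say which.
3. Keep the SRM, if desired, as a descriptive figure per session, and state that SRMs are not to be compared between conditions.

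The cost is a few sentences and a short calculation on data the crossover already yields. No extra visits, measurements or participants are needed.
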